### Estimation of the household costs

Direct treatment costs reported by the households for each of the individual components will be compared, and data quality checks will be performed. Expenses incurred by households for each component will be estimated per SYI, based on the number of households in the sample after removing outliers. Outliers will be flagged using the median-absolute deviation and values exceeding plausible ranges (*e.g.* food costs exceeding World Bank *food per capita* benchmarks and wage losses based on World Bank *per capita* benchmarks).Household expenses included for CEA will be for registration/ consultation, recommended medications (gentamicin, ampicillin, amoxicillin), recommended consumables (syringes + needles, cotton swabs and CRP (for RCT2)), transport, food and wage loss. All other non-recommended treatments for which households incur expenditure as part of the PSBI treatment will be reported as an additional burden.For each treatment arm, total transport expenses will be added for all days (maximum seven) that transport is used by any caretaker for round-trip travel, and this is then divided by the number of sampled households after conducting the quality checks and removing outliers.For food charges, a similar method of estimation will be used as for transport expenses. Total expenses reported by any caretaker during the treatment period will be summed and then divided by the number of households in the sample, after removing outliers.Wage loss will be calculated per family or per SYI for each of the treatment arms.Average wage/day will be calculated even when annual or monthly wages are given. The average wage for each caregiver will be the average of the range.Average wage/day for each caregiver will be multiplied by the number of days lost for a SYI for any treatment. Maximum days lost by any caretaker will be capped at seven days of recommended treatmentSum of the total wage loss for a family for all caretakers combined will be (A) under any treatment arm.Sum of the number of families that report positive or zero wage loss for any of the caretakers will be (B). SYI where family members did not provide consent will be excluded from the denominator for calculations.Total wage loss per SYI or per family under each treatment arm = A / B

All recommended or non-recommended medical and non-medical costs will be calculated per SYI as an additional burden on households.

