
#### Household cost data

Household expense data will be collected during the last nine months of the study at each site to capture the out-of-pocket expenditures that households incur during the treatment of enrolled SYI under both treatment arms for RCT1 and RCT2. Data will be collected from at least 10% of SYIs enrolled under each arm at each site. These sampled households will be assumed to be representative of all treated YIs both temporally and geographically. Further, the household data for the seven-day treatment period will be collected either on day eight or 15 of the outcome visit or at most within two weeks from the last outcome assessment, to avoid recall bias. Where available, caregiver-reported expenditures will be cross-checked with receipts or facility payment records to enhance accuracy.Standardised household questionnaires will be used across all sites to collect data on medical and non-medical costs using the REDCap tool [25,26]. Training will be provided to collect data using these forms, and pilots will help improve the tool and data quality. Data inconsistencies will be identified, discussed with the sites and corrected at the analysis stage.Data will be collected on the type of treatment arm and duration of treatment. Direct treatment costs for each component will be collected in local currency from sampled households in each treatment arm for RCT1 and RCT2 at each site. Total medical expenses by households will be collected for registration and consultation fees, expenditures on medicines such as amoxicillin, ampicillin, gentamicin and other supportive care such as paracetamol, consumable supplies such as syringes, needles, canulas, bandages, spirits, gloves, laboratory expenses such as x-ray, blood work, urine tests (investigation costs), or any other payments to hospitals. Non-medical expenses, such as transport and food, will be recorded for seven days. Data will include the mode of transportation and expenses incurred by any household member on round-trip trips during the treatment period. Similar information will be collected on food, with the amount spent outside the home during the days the infant had to stay at or visit the hospital.Indirect expenses are opportunity costs, or the costs incurred by the household in terms of wage loss to take care of the sick child. Data will be collected from parents and caretakers who lost their wages due to time spent caring for the child. Household work that does not entail income will not be included in the opportunity cost. Data will be collected on the type of occupation/source of income, average earnings on a daily, monthly, or yearly basis (in the provided ranges), and the number of days not able to work to take care of the SYI. Maximum seven days of wage loss will be considered.

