
### Estimation of hospital operational costs

Data collected for hospital indirect cost components – training, communications and supplies – are annual and relate to all infants assessed for PSBI during that year. For each site, expenses for training, communications and supplies will be added across facilities. The number of infants assessed during a year at a hospital will be estimated based on the total number of infants assessed over the entire study period and proportionally for 12 months. The sum of expenditures for each component will be weighted by the number of SYI assessed at each hospital for PSBI during the year to obtain the weighted expense per SYI at each site.Inpatient bed costs are shared costs across all infants and children admitted to newborn intensive care units and paediatric wards for shared items such as non-consumables, utilities, laundry, security, administration and other departmental expenses. The costs per admitted child will be estimated by dividing the total annual administrative expenditures (exclusive of staff costs, medicines, and consumables costs for enrolled SYI) of the paediatric and newborn intensive care units by the total number of children admitted in that year. These will be adjusted proportionately based on the average length of stay for enrolled SYI with PSBI relative to other SYI admitted during the year. We assume there are no inpatient bed costs for the intervention arm (outpatient) under RCT1 and for the 5-day ambulatory treatment in RCT2.Hospital transport/ambulance costs may be incurred for some patients brought to the hospital by public ambulance. Since it is difficult to obtain the data from the hospital database for each SYI enrolled, an indirect estimation method will be used. Household survey data will be used to determine the proportion of SYI who report using free public transport under different RCT treatment arms. Each site will calculate the average cost per trip based on the average distance to the hospital and the cost per km or mile. The cost per km depends on drivers' salaries, fuel costs for the average distance to hospitals in the study area, and vehicle maintenance costs at the site. Multiplying the average costs by the estimated number of SYI using public transport under each arm will provide an estimate of transport costs incurred at the hospital level.

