### Strengths and limitations

We integrate economic and clinical evidence to identify safe, cost-efficient treatment strategies that could reduce economic burdens, inform national budgeting decisions, and potentially support revisions to WHO guidelines for improved infant care in low-resource settings worldwide.

A key strength is that the analysis is embedded within a multi-country RCT and incorporates both provider and household perspectives to assess CE from societal and provider/payer perspectives. The use of site-level stratification and INB methods further enhances transparency in quantifying uncertainty and supports decision-making using threshold-based interpretation.

Hospital cost data will be collected from all hospitals that randomise infants into treatment arms and aggregated across sites. Provider and household cost data will be collected over a consistent, recent financial period, ensuring alignment of price inputs and minimising variability due to inflation or exchange rate fluctuations during the multi-year enrolment period. Household expenditures will be collected close to the time of care (day eight, 15, or within two weeks after the 15-day outcome visit), with cross-verification against receipts or facility records where available, thereby reducing recall bias. Provider cost and outcome analyses will include the full randomised cohort, strengthening the robustness of the primary CE estimates.

One limitation is that household costs and wage data will be collected during the final nine months of the study using a purposive sample of approximately 10–15% of enrolled infants in each treatment arm at each site. Although this improves operational feasibility, it may introduce selection bias when estimating non-medical costs if respondents differ systematically from those not interviewed. No imputation or adjustment methods will be applied; although missing data are assumed to be random, non-random patterns cannot be entirely ruled out.

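### Household costs flagged by median-absolute deviation are deleted before averaging without being shown to be errors, which biases mean household cost downward

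*Protocol article*

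**What the plan says.** Under Estimation of the household costs, the expense for each component is estimated per infant "based on the number of households in the sample after removing outliers". The flagging rule is: "Outliers will be flagged using the median-absolute deviation and values exceeding plausible ranges". The two examples of plausible ranges, for food and wage loss, are upper limits taken from World Bank per capita benchmarks. Removal is repeated for transport, where the total is "divided by the number of sampled households after conducting the quality checks and removing outliers", and food is handled in a similar way. No multiplier, measurement scale or treatment of zeros is stated, nor whether one flag alone is enough.

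The article shows where zeros arise. Families reporting zero wage loss are counted in the wage-loss denominator. Under Household cost data, "Household work that does not entail income will not be included in the opportunity cost". Under Estimation of hospital operational costs, the household survey supplies "the proportion of SYI who report using free public transport under different RCT treatment arms".

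Under CEA, the ratio is the difference in mean costs divided by the difference in effectiveness. The net benefit uses the same cost difference. Household transport, food and wage loss are part of the societal cost.

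**The concern.** A cost-effectiveness analysis needs the arithmetic mean, because the mean times the number of infants gives the total bill. A genuine high cost is part of that bill.

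A median-absolute-deviation (MAD) rule sets limits at equal distances above and below the median. With a right-skewed, non-negative cost the lower limit can fall below zero, where no observation lies. All deletions then come from the upper tail, and the mean can only fall. The listed plausible-range examples also cut only at the top.

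Zeros make this worse. As their share nears one half, the median and the MAD both shrink towards zero and ordinary positive costs are flagged.

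At stake are the mean household costs, the household burden reported as a result in its own right, and the societal ratio and net benefit. Hospital-collected staff, medicine, consumable and bed costs are not subject to this deletion.

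**Working it through.** The article states no figure on this point, so there is none to reproduce. The inputs below are assumptions, shown over a range.

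**Rule.** Delete a value x if |x − median| > k × 1.4826 × MAD. The article gives no k, so k = 2.5 to 5 is tried, with k = 3 as the central case.

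**Costs without zeros.** Assume lognormal costs with mean 1 and log-scale standard deviation s. Then CV = √(exp(s²) − 1) and the median is exp(−s²/2). The MAD solves F(median + MAD) − F(median − MAD) = 0.5, where F is the lognormal distribution function. The mean after deletion is the share of total cost kept divided by the share of households kept.

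For CV 1, s = √(ln 2) = 0.833, median = 0.707 and MAD = 0.365. With k = 3 the limits are 0.707 ± 3 × 1.4826 × 0.365, that is −0.92 and 2.33. The lower limit is negative, so only high values go. Kept are 92.4% of households and 72.6% of cost, so the new mean is 0.726 / 0.924 = 0.785, a fall of 21.5%.

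| Assumed spread (k = 3) | Upper limit | Households removed | Fall in mean |
|---|---|---|---|
| CV 0.5 (s = 0.47) | 2.13 | 3.3% | 5.5% |
| CV 1 (s = 0.83) | 2.33 | 7.6% | 21.5% |
| s = 1.0 (CV 1.31) | 2.22 | 9.7% | 32% |

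At CV 1 the fall is 25% for k = 2.5 and 12% for k = 5. A lenient cut-off reduces the bias but does not remove it.

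**Costs with zeros, CV 1 among positive values, k = 3, rule applied to all households (simulation).**

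| Share of zeros | Fall in mean |
|---|---|
| 30% | 22% |
| 40% | 35% |
| 45% | 49% |
| 49% | 73% |
| more than 50% | 100% |

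Above one half, median = 0 and MAD = 0, so every positive value is flagged whatever k is. With 11 zeros among 20 families, all 9 positive values go and the mean drops from 4.15 to 0. At exactly half the loss need not be complete: in an example with 10 zeros among 20, 6 of the 10 positive values go.

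**Other readings of the rule (CV 1, k = 3).** With the MAD taken over positive values only, the mean falls by 23% to 25% at zero shares of 30% and 60%. If both flags must be met, with an assumed plausible-range cap of 3 to 5 times the mean positive cost, it falls by 5% to 17%. Neither reading makes the mean collapse to zero, and both still bias it downward.

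**Effect on the difference between arms.** If both arms fall by 21.5%, the household cost difference becomes 0.785 × (C₁ − C₂), so a real saving is understated by 21.5%. If the arms differ in their share of zeros, the error can go the other way. With a mean positive cost of 20, CV 1, and assumed zero shares of 40% (control) and 60% (intervention), the full-data means are 12.0 and 8.0, a difference of −4.0. After deletion they are 7.8 and 0.0, a difference of −7.8. This only illustrates that the bias need not cancel.

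**The case against.** The strongest reply is that the article leaves the cut-off, the scale, the handling of zeros and the combination of flags open, and such detail commonly sits in a fuller plan. That stands against the collapse result, which holds on one reading only. It does not answer the main point, because removal before averaging is stated outright and biases the mean downward on every reading tried.

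A second reply is that the tail may be modest. Wage loss is capped at seven days, earnings are taken as the average of a range, and transport and food cover seven days. This stands as a limit on size, and the 5.5% case may be nearer the truth for some items. The calculation also treats every flagged value as genuine. Some will be recall or entry errors, and deleting those is useful.

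Third, checks already exist. Household cost data provides for comparison with receipts or facility records where available and for correcting inconsistencies with the sites. Both median and mean will be reported. These checks are sound, but the article does not make removal depend on them.

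Two stronger readings are tempting. A reader might infer that the rule will wipe out wage loss or transport in this trial, or that it favours one arm. The article reports no zero share for any item, site or arm, so neither is supported. A reader might also add the survey sample to the charge, since "These sampled households will be assumed to be representative of all treated YIs both temporally and geographically" sits beside "No imputation or adjustment methods will be applied". That is a separate limitation which the article discloses, and it is no part of this point.

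**Conclusion.** The concern holds in this form: the plan deletes flagged household costs before averaging without requiring evidence of error, and for right-skewed costs this biases the mean household cost and the household burden downward. The societal ratio and net benefit carry the error, but its direction in the difference between arms cannot be told from the article.

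The direction for the means rests only on right skew, which is likely for such costs though the article does not show it. The size rests on assumed lognormal costs, a cut-off of 3 scaled deviations and flagged values being genuine: about 5% at CV 0.5, 22% at CV 1 and 32% at a log-scale standard deviation of 1.0, and more with many zeros. Complete loss of positive values needs three conditions together: more than half zeros, the rule applied to all households including zeros, and either flag sufficing. The article fixes none of them.

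**What to change.** Use the two flags only to trigger queries against receipts, facility records or the site. Correct or drop a value only when it is shown to be an error, and report the number corrected or dropped by item, arm and site. Make the arithmetic mean over all surveyed households with verified or unrefuted values, zeros included, the primary estimate for the societal ratio, the net benefit and the household burden. Report a winsorised or trimmed mean as a sensitivity analysis, with its cut-off and its handling of zeros fixed in advance.

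The change affects the analysis and data queries only. The cost is that the means will be somewhat less stable, and some recall errors that cannot be checked will stay in.

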### CEA

CE will be evaluated by estimating the ICER, defined as the difference in mean costs between the intervention and control arms divided by the difference in effectiveness between the two arms: ICER = (C_1_ − C_2_) / (E_1_ − E_2_), where C_1_ are the average costs for the intervention group; C_2_ are the average costs for the control group; E_1_ is the mean effectiveness measure for the intervention group, and E_2_ is the mean effectiveness measure for the control group. We will use societal costs – hospitals and households’ – medical costs (staff time, medicines, consumables); hospital inpatient bed cost, operational costs and households’ non-medical costs (transport, food and wage loss) for ICER calculations for all randomised SYI in both arms. We will also report ICER from only the provider/payer perspective using only medical costs for all enrolled SYI and those receiving at least 80% of the recommended seven-day treatment as a sensitivity analysis [27].

For RCT2, while the baseline costs will be presented for both pre- and post-randomisation for both study arms, the costs for ICER calculations will be compared only post-randomisation.

For each RCT, cost measures will be evaluated in both the control and intervention arms for all enrolled infants who receive either the full seven-day treatment or partial treatment. Effectiveness will be assessed in the same population based on clinical outcomes recorded on days two (for RCT1), four, eight, and 15 following treatment initiation. The ICER will be calculated for each RCT to assess whether the intervention is more cost-effective than the control.

There can be 4 case scenarios for ICER (**Figure 2**):

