**Methods:**

Cost analysis will be conducted from societal (hospital and household) perspectives. Hospital medical costs (staff, medicines, and consumables) and operational costs (inpatient bed costs, non-consumables, training, and communication) will be collected through hospital surveys. Household costs, including medical payments for treatment (registration, consultations, medications, consumables) and non-medical costs (transport, food, and wage loss), will be collected through household surveys. In both RCTs, combined hospital and household (including medical and non-medical) costs for all randomised sick YIs (SYIs) will be used, with an intention-to-treat approach, to calculate the cost per SYI in each study arm. Effectiveness measures, based on the absence of adverse outcomes, will be used to determine incremental CE ratios and incremental net benefits. Separate societal and payer/provider perspectives will be considered, and site-specific willingness-to-pay thresholds will be estimated. The household’s medical and non-medical costs, along with their share of societal costs, will estimate the household burden per treated child.

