### Costs framework

The cost will be assessed from both the hospital and household perspectives. From the hospital perspective, medical treatment costs will be determined at each study hospital across all sites in both the intervention and control arms (**Table 1**, **Table 2**). Additionally, the household's costs will be separated into medical and non-medical costs. The hospital's indirect operational costs and households' opportunity costs in terms of wage loss will also be estimated. The costs will be weighted by infant days for each hospital, separately for the control and intervention arms, to obtain site-specific average costs for each item. To generate combined estimates, we will pool site-specific average costs across all sites to produce a single multi-country mean cost for inpatient and outpatient management, respectively.

**Table 1 T1:** Framework for provider costs under RCT1: outpatient versus inpatient management of young infants (0–59 days) with low-mortality-risk PSBI signs

Cost category	Intervention arm: outpatient treatment	Control arm: inpatient treatment
Place of treatment	Outpatient/ambulatory care	Hospital inpatient care
Antibiotic regimen	Injectable gentamicin once daily for 2 days plus oral amoxicillin twice daily for 7 days	Injectable ampicillin (2–4 times daily depending on age) plus injectable gentamicin once daily for 7 days
Staff costs	Outpatient assessment, counselling, injections preparation (canula), gentamicin administration, follow-up visits	Inpatient assessment, nursing care, injections preparation (canula) + administration, monitoring and supportive care
Medicine costs	Gentamicin and oral amoxicillin	Ampicillin and gentamicin
Consumables	Syringes, needles, cotton swabs, gloves, cannula, spirit	Syringes, needles, intravenous supplies, cotton swabs, gloves, cannula, spirit
Inpatient bed costs	Not applicable	Included for the duration of hospitalisation. Captures costs in the paediatric wards, such as costs of non- consumables, utilities, security, and laundry
Operational and indirect costs	Training, supervision, communication, administration and programme support	Training, supervision, communication, administration and programme support
Weighting approach for pooled analysis	Infant-days (number of infants treated and days each medicine or consumable is used)	Infant-days (number of infants treated and days each medicine or consumable is used)

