
### Statistical analysis procedures

The statistical analysis for the hospital cost data will be done in Microsoft Excel (Microsoft, Redmond, WA, USA). The data from all facilities where infants are randomised will be entered into a structured Excel document. The average costs per SYI for staff, medicines, consumables, and inpatient bed costs, will be calculated as outlined below. Mean, median, and 95% confidence intervals will be calculated using t-values per SYI receiving recommended or partial treatment for each of the cost variables at the hospital, as well as at the household level. The medical treatment costs per SYI will be the sum of the weighted average of staff costs, medicines, consumables, inpatient bed costs, and operational costs, where weights are infant-days for those receiving recommended and partial treatment. Non-medical costs on transport, food and wage loss per SYI will be added to total medical costs per SYI to estimate the total societal costs for the control and intervention arms for RCT1 and RCT2 separately. Household payments for both medical and non-medical treatment would be added to calculate the household burden in total societal costs.

The treatment outcomes for all enrolled in the control and intervention arms will be used to estimate incremental CE ratios (ICERs) for both RCTs.

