## DISCUSSION

We present a detailed methodological framework for estimating the costs of managing PSBI in YIs, integrating both health system and household perspectives across different contexts. To our knowledge, we are the first to comprehensively assess both economic and clinical outcomes using such a dual-perspective approach. By analysing medical treatment costs – including staff time, medicines, consumables, inpatient bed costs, and indirect operational costs – as well as non-medical costs such as transport, food, and wage loss, our framework captures the full economic burden faced by hospitals and households. The methodology enables comparison of costs for treating low-mortality-risk PSBI in both hospital and outpatient settings, as well as moderate-mortality-risk PSBI in YIs under shorter and longer hospital stays.

By establishing a standardised approach to CEA using both ICERs and INB, and by incorporating both societal and payer perspectives, the framework supports robust evaluation of RCT outcomes. This approach strengthens evidence-based decision-making and policy formulation. The findings from this study have the potential to reshape PSBI management guidelines and support a paradigm shift in PSBI care. If outpatient treatment for YIs with low-mortality-risk PSBI signs and shorter hospital stays for moderate-mortality-risk cases are shown to be safe and cost-effective, these strategies could substantially reduce both household and health system costs while improving access to care in resource-constrained settings. Policymakers, providers, and payers would benefit from these insights.

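### "Medical costs" carries two incompatible definitions, so the protocol does not settle whether the secondary provider/payer ICER includes inpatient bed and operational costs

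*Protocol article*

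**What the plan says.** The CEA section of the protocol article specifies two ICERs.

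- The main one is societal. Its cost list includes "medical costs (staff time, medicines, consumables); hospital inpatient bed cost, operational costs", followed by household non-medical costs.
- The second is introduced in the next sentence: "We will also report ICER from only the provider/payer perspective using only medical costs for all enrolled SYI", and also for infants who received at least 80% of the recommended treatment. No component list is given for it.

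Elsewhere the term is used in two ways.

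- **Narrow.** The abstract has "Hospital medical costs (staff, medicines, and consumables) and operational costs (inpatient bed costs, non-consumables, training, and communication". Bed cost is operational there, not medical.
- **Broad.** The statistical analysis procedures state: "The medical treatment costs per SYI will be the sum of the weighted average of staff costs, medicines, consumables, inpatient bed costs, and operational costs". The Discussion describes medical treatment costs as "including staff time, medicines, consumables, inpatient bed costs, and indirect operational costs". Tables 1 and 2 in the costs framework, both titled as provider-cost frameworks, each have a row for inpatient bed costs and a row for operational and indirect costs.

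On how bed cost falls between arms, Table 1 has it not applicable to the RCT1 outpatient arm and "Included for the duration of hospitalisation" for the control arm. The section on hospital operational costs adds: "We assume there are no inpatient bed costs for the intervention arm (outpatient) under RCT1 and for the 5-day ambulatory treatment in RCT2".

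**The concern.** The provider/payer ICER is defined by a single term, and the protocol gives that term two meanings. The narrow meaning stands in the sentence directly before the one that defines this ICER, so an analyst working from the CEA section alone would leave bed cost out. An analyst working from the statistical analysis procedures would put it in.

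The choice is not neutral between arms. Bed overhead is the disputed item that differs most by design: it is charged for inpatient days and set to zero for outpatient days. Both trials compare a hospital stay with a shorter stay or none, and the hypothesis section gives relief of hospitals and better use of their resources as a purpose. A provider result without ward overhead would understate the saving to the hospital. The contrast between the societal and provider perspectives would then mix a change of perspective with the loss of a hospital-borne cost. The protocol presents having both perspectives as a key strength, so the second needs a fixed content before results are seen.

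**Working it through.** The protocol states no figure for this point and no bed cost per day, so the check compares definitions and then works out the effect in symbols.

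**Step 1. Definitions side by side**

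| Place | Bed and operational costs inside medical (or provider) costs? |
|---|---|
| Abstract, Methods | No; bed cost is placed under operational costs |
| CEA, societal cost list | No; listed separately after the bracket |
| Costs framework, Tables 1 and 2 (provider costs) | Yes |
| Statistical analysis procedures | Yes |
| Discussion | Yes |

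**Step 2. Can the two be reconciled as different terms?** One could suppose that medical costs and medical treatment costs are meant to differ. The statistical analysis procedures rule this out: "Non-medical costs on transport, food and wage loss per SYI will be added to total medical costs per SYI to estimate the total societal costs". The CEA section puts bed cost in the societal total. If only non-medical items are added to reach that total, then total medical costs must already contain bed cost. The conflict with the CEA bracket is therefore real.

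**Step 3. Which disputed items move the cost difference?** Training, supplies and communication are estimated per infant assessed, so within a site they largely cancel between arms. Bed cost does not cancel.

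**Step 4. Size.** Let b be bed cost per day (not given; any b > 0). Assume that charged bed-days follow the protocol's nominal treatment periods. Let p be the control-arm proportion counted as having received recommended treatment (not given).

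- Infants with at least 80% of treatment, counted as full treatment:
  - RCT1: control 7b, intervention 0; difference 7b.
  - RCT2 (ICER costs are post-randomisation only): control 5b, intervention 0; difference 5b.
- All enrolled, with partial treatment costed at three days in RCT1 and two post-randomisation days in RCT2:
  - RCT1: B = b × [7p + 3(1 − p)] = b × (3 + 4p), from 3b at p = 0 to 7b at p = 1.
  - RCT2: B = b × [5p + 2(1 − p)] = b × (2 + 3p), from 2b at p = 0 to 5b at p = 1.

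**Step 5. Effect on the results.** With Δc = C1 − C2 and Δe = E1 − E2:

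- Δc(narrow) = Δc(broad) + B, apart from the small non-cancelling part of the other disputed items.
- ICER(narrow) − ICER(broad) = B/Δe.
- INB = λΔe − Δc, so any INB from the provider perspective falls by B.

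For any b > 0, leaving bed cost out makes the intervention look less cost-saving to the provider. If the broad definition governs, the shift is zero.

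**Step 6. Other loose ends in the same term.**

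- Hospital ambulance transport is described under hospital data as a cost to the hospital. It is in neither cost definition, nor is it one of the three operational items named there (training, supplies, communication).
- The CEA cost list speaks of medical costs of hospitals and households together, so it is also open whether household medical payments enter a provider/payer ICER.

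**The case against.** The strongest reply is that the document as a whole favours inclusion. The tables titled as provider costs contain bed and operational rows, and the costs framework ties medical treatment costs from the hospital perspective to those tables. The societal sum in the statistical analysis procedures works only if bed cost counts as medical. In the CEA sentence the contrasting label is household non-medical costs, so restricting to medical costs may simply mean dropping transport, food and wage loss. All of this stands. It means the omission is not established. It does not remove the conflict, because the narrow bracket is in the very paragraph that defines the provider/payer ICER, and nothing says which definition governs.

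Three stronger readings may tempt a reader and are not supported.

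- **That the hospital stay is costed at nothing.** Under either definition, inpatient nursing, monitoring, injections, medicines and intravenous supplies are costed. Only shared ward overhead (utilities, laundry, security, administration, non-consumables) is at stake.
- **That a known share of the saving is lost.** With S the saving in staff, medicines and consumables, the share would be B/(B + S). Taking B between 0.5 and 2 times S gives 0.5/1.5 = 33% to 2/3 = 67%. The protocol gives neither B nor S, so these percentages only restate the assumed ratio.
- **That the main result is affected.** The societal ICER names inpatient bed cost explicitly.

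It is also fair to say that the possible error runs against the intervention and that the affected ICER is an additional report.

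**Conclusion.** The point holds as an internal contradiction. The abstract and the CEA section exclude bed and operational costs from medical costs; the statistical analysis procedures, the Discussion and the provider-cost tables include them. The cost content of the provider/payer ICER is therefore not fixed. A reader might infer that bed cost is certainly omitted, but the documents do not settle that.

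If the CEA wording is followed literally, the provider saving is understated by about 7b in RCT1 and 5b in RCT2 for infants counted as fully treated, and by less for all enrolled infants. If the broad definition is followed, the shift is zero. The day counts assume that bed-days follow the nominal treatment periods. The direction requires only b > 0. The monetary size cannot be given.

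The consequence is limited to a secondary analysis. The matter should still be settled before that ICER is computed, since the protocol reports data collection as complete and an open definition could be chosen with results in view.

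**What to change.** In the CEA section, replace the reference to medical costs in the provider/payer sentence with an explicit list: all provider-borne costs in Tables 1 and 2 (staff, medicines, consumables, inpatient bed, operational) plus hospital-borne ambulance cost. State whether household medical payments are included under the payer label.

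Then use one definition of medical costs in the abstract, the costs framework, the statistical analysis procedures, the CEA section and the Discussion. If the narrow definition is kept, the societal sum in the statistical analysis procedures must be reworded to add bed and operational costs by name; otherwise the societal total would lose them.

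The cost is wording only. Every hospital component is already planned for collection, or for indirect estimation in the case of ambulance cost, and household medical payments are already in the household survey.
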